#### 2.1.2 Secondary objective

The secondary objective of this study was to identify differential metabolites in the serum and urine of patients before and after JTTF treatment to determine possible relevant metabolic pathways and routes of action in T2DM combined with NAFLD. Furthermore, we explored the regulatory effects and mechanisms of JTTF action on various aspects including lipid and glucose regulation at the metabolic level.

### 2.2 Study design

This study is designed as a 12-weeks, single-center, double-armed, parallel, randomized, controlled clinical trial. A total of 96 eligible participants will be recruited from Shenzhen Hospital of Guangzhou University of Chinese Medicine (Futian) and randomized in a 1:1 ratio into two groups to receive basic treatment. As a supplement to the clinical study, participants’ fasting serum and urine samples will be subjected to untargeted and targeted metabolomic assays. Liquid chromatography–mass spectrometry (LC-MS) will be used to compare metabolites before and after treatment in the experimental and control groups. Basic analysis of metabolites, multivariate statistical analysis, pathway enrichment analysis, and topological analysis of the screened differential metabolites will be performed.

All patients should have voluntarily participated and signed an informed consent form with good compliance. Informed consent will be obtained from all participants prior to enrollment. A flowchart and schedule of the clinical trial is shown in Figure 1 and Table 1, respectively. The protocol was designed according to the Standard Protocol Items: Recommendations for Interventional Trials (SPIRIT) guidelines (Chan et al., 2013) and the Declaration of Helsinki. The SPIRIT checklist is shown in Supplementary Material S2.

**FIGURE 1 F1:**
[figure not shown]
Flow chart of the clinical trial.

**TABLE 1 T1:** Schedule of the clinical trial.

Project time	Screening/baseline		Treatment			
	-14–0 days	0±2 days	Visit 1 4weeks± 2days	Visit 2 6weeks± 4days	Visit 3 8weeks± 6days	Visit 4 12weeks± 7days
Eligibility screening						
Inclusion/exclusion criteria	**✓**					
Informed consent form	**✓**					
Allocation	**✓**					
General information	**✓**					
Family history	**✓**					
Medical history	**✓**					
Drinking history	**✓**					
Physical examination^a^	**✓**	**✓**	**✓**	**✓**	**✓**	**✓**
Vital signs^b^	**✓**	**✓**	**✓**	**✓**	**✓**	**✓**
Ultrasound of liver	**✓**					**✓**
bioelectrical impedance analysis						
visceral fat area		**✓**				**✓**
subcutaneous fat area		**✓**				**✓**
Electrocardiography	**✓**			**✓**		**✓**
Laboratory examination						
Routine blood test		**✓**		**✓**		**✓**
Routine urine test		**✓**		**✓**		**✓**
Fasting blood sugar		**✓**		**✓**		**✓**
2-h plasma glucose		**✓**				**✓**
Glycated hemoglobin		**✓**				**✓**
Fasting insulin		**✓**				**✓**
Blood lipids		**✓**		**✓**		**✓**
Liver function		**✓**		**✓**		**✓**
Renal function		**✓**		**✓**		**✓**
Traditional Chinese medicine symptoms		**✓**	**✓**	**✓**	**✓**	**✓**
Fibrosis 4 Score		**✓**				**✓**
Homeostasis model assessment-insulin resistance		**✓**				**✓**
homeostatic model assessment for β-cell		**✓**				**✓**
Metabolomics test^c^						
Serum sample		**✓**				**✓**
Urine sample		**✓**				**✓**
Adverse event			**✓**	**✓**	**✓**	**✓**
Prescription		**✓**	**✓**	**✓**	**✓**	**✓**
Combined drugs		**✓**	**✓**	**✓**	**✓**	**✓**
Summary of the analysis						**✓**

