#### 2.8.2 Primary outcomes

The primary outcome is change in visceral fat area (VFA) and TCM syndromes efficacy score scale. Changes in VFA will be compared between the two groups before and after treatment. The indicator will be tested at baseline and week 12. The TCM symptom scoring standard is presented in Supplementary Material S3.

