### 2.9 Randomization and data collection

Patients successfully enrolled in the study will be randomly assigned to either the treatment or control group at a 1:1 ratio. The randomization sequence number will be sealed in an opaque envelope and provided only to clinicians so that the participants can be assigned to the treatment regimen accordingly. Since this trial is an open-label study, participants and physicians will be aware of the assignment protocol, whereas data analysts and statisticians will not be aware of the distribution results.

In this study, all participants’ data will be collected, recorded, and administered in the CRF provided by the Ethics Committee of Shenzhen Hospital of Guangzhou University of Chinese Medicine (Futian). Data from the original CRF and biological samples will be stored for an additional 5 years after the trial ends.

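### Table 1 puts open-label allocation in the screening column and the first TCM score and VFA in the next, so baselines may be recorded after the arm is known

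*Protocol article*

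**What the plan says.** **Schedule (section 2.2, Table 1).** Two columns sit under the Screening/baseline header: day -14 to 0, and day 0±2.

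- Allocation has one tick, in the first column, with consent and the eligibility criteria.
- The rows "visceral fat area" and "Traditional Chinese medicine symptoms" have no tick in the first column. Both are first ticked at day 0±2.
- The glucose measures, HbA1c, liver and renal function, and the serum and urine metabolomics samples also start at day 0±2.
- The row "Prescription" is first ticked in that same second column.

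**Outcome (section 2.8.2).** "The primary outcome is change in visceral fat area (VFA) and TCM syndromes efficacy score scale". On timing, the text says of VFA only that "The indicator will be tested at baseline and week 12". It does not place baseline before allocation.

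**Randomisation and masking (section 2.9).** "Patients successfully enrolled in the study will be randomly assigned to either the treatment or control group at a 1:1 ratio". The assignment is kept in opaque envelopes given to clinicians, and no opening day is stated. "Since this trial is an open-label study, participants and physicians will be aware of the assignment protocol". Only data analysts and statisticians are masked.

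**The concern.** A change-from-baseline endpoint is protected by randomisation only if the baseline is fixed before the arm is known. Read in column order, this schedule has patient and physician learn the arm and then score the symptoms that form the baseline of a primary outcome. A patient who expects the formula, or a physician who knows it will be given, may report or rate symptoms differently. That difference then becomes part of the apparent treatment effect.

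Two usual safeguards do not help. Masked analysts receive data that already contain the shift. Adjusting for baseline does not restore balance either, because such a baseline is no longer a pre-randomisation variable.

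VFA is a bioelectrical impedance reading, and the laboratory values are instrument results. They are affected mainly if behaviour or treatment changes before they are taken.

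**Working it through.** The plan states no figure on this point, so there is none to reproduce. The check has three parts.

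**1. What the two windows permit.** Allocation may fall on any of 15 days (-14 to 0) and baseline on any of 5 days (-2 to +2), which gives 15 × 5 = 75 day pairs.

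| Order | Pairs |
|---|---|
| Baseline after allocation | 69 |
| Same day | 3 (days -2, -1, 0) |
| Baseline before allocation | 3 (allocation day 0 with baseline day -2 or -1; allocation day -1 with baseline day -2) |

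The largest gap is 2 - (-14) = 16 days. Two of the five permitted baseline days, +1 and +2, come after day 0. This count describes what the table allows. It is not a probability.

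**2. Whether other text restores the order.** Sections 2.8.2 and 2.9 do not. The eligibility rules point to the same fault. Section 2.5 excludes on AST, ALT and creatinine, and section 2.4 uses FPG, 2-h PG, HbA1c and TCM symptoms. Table 1 ticks the eligibility criteria in the first column, yet first schedules all of these measurements in the second, after the Allocation column.

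**3. What a shifted baseline would do (illustration).**

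Inputs:
- 38 evaluable per arm, from the 76 patients required in section 2.10 divided by 2.
- Assumed, with no source in the document: no true effect; equal SDs at baseline and week 12; correlation r = 0.5 between them; a t-test on change; and a between-arm baseline shift of δ SD that has gone by week 12.

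Formulas:
- Expected between-arm difference in change = 0 - δ, so its size is δ.
- SD of change = √(2(1 - r)) = √(2 × 0.5) = 1 raw SD.
- Non-centrality = δ × √(38/2) = δ × 4.359, with df = 2 × 38 - 2 = 74 and critical t = 1.993.

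| δ (SD) | Non-centrality | Two-sided rejection rate, no true effect |
|---|---|---|
| 0 | 0 | 5% |
| 0.1 | 0.436 | 7.1% |
| 0.2 | 0.872 | 13.8% |
| 0.3 | 1.308 | 25.2% |

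The result depends on r through the SD of change. At δ = 0.2, r = 0.3 gives SD √1.4 = 1.183 and a rate of 11.2%; r = 0.7 gives SD √0.6 = 0.775 and a rate of 19.9%.

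Baseline adjustment under the same assumptions subtracts about r × δ instead of δ. At r = 0.5 and δ = 0.2, a bias of 0.5 × 0.2 = 0.1 SD remains. Adjustment reduces the bias here but does not remove it.

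**The case against.** The strongest reply is that the table is loosely laid out and does not prescribe a post-allocation baseline. Several parts of this stand.

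- **The columns overlap on days -2 to 0.** A site that measures first and allocates later the same day complies. A reader might infer that every baseline is taken after allocation; the document does not support that.
- **The arm may be disclosed later than the tick suggests**, since no day is given for opening the envelope. Figure 1, which could show the order, is not visible here.
- **Both columns sit under Screening/baseline**, and adverse events are first recorded at Visit 1. The layout thus presents day 0±2 as a pre-treatment visit. Day 0 is not defined as the first dose, so a reader who infers that baselines do follow treatment goes too far. The +2 day window and the shared column with the first prescription only fail to rule it out.
- **VFA is much less exposed than the TCM score**, and section 2.7 gives both arms the same lifestyle management. Treating the two primary outcomes as equally at risk would be too strong.
- **The inflation figures are hypothetical.** Section 3.1 does not say whether the between-group test uses changes or final values, and section 2.8.2 spells out a comparison of changes only for VFA. If week-12 TCM scores alone were compared, a baseline shift would not enter that test.
- **The TCM score remains unmasked at every later visit.** Correcting the order does not cure that.

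None of this supplies the missing rule. The order shown in the table is unfavourable, and no visible text overrides it. If the tick is merely misplaced, the table still needs correcting, because sites follow the schedule.

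**Conclusion.** The point holds as a fault in the stated order. Table 1 implies and permits baseline values recorded up to 16 days after open-label allocation, and it does not exclude a baseline after the first dose. It does not force either.

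The material risk is to the TCM score. For VFA, the laboratory values and the metabolomics samples, the risk is smaller and depends on behaviour or treatment changing first.

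The false-positive rates of about 7%, 14% and 25% show how sensitive a change-score test with 38 per arm would be to shifts of 0.1, 0.2 and 0.3 SD. They do not estimate the bias in this trial, because neither the shifts nor the correlation comes from the document.

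The correction is worth making promptly. Section 5 reports that recruitment was under way, and a compromised baseline cannot be retaken.

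**What to change.** **For patients not yet randomised:**
- Move the Allocation tick in Table 1 to day 0, after all baseline and eligibility assessments.
- State in section 2.9 that the envelope is opened, and study treatment dispensed, only once the baseline TCM score, VFA, blood and urine samples are complete.
- Change the baseline window so that it ends at allocation, for example day -2 to 0.

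**For patients already randomised:**
- Record and report the dates of allocation, baseline and first dose.
- Add a supportive between-arm comparison of week-12 values that does not use the affected baseline.
- Do not exclude patients whose baseline followed allocation. That would be a post-randomisation exclusion and could remove nearly everyone.

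**Cost:** one table edit, a sentence or two of procedure, and one supportive analysis. No visit, test or patient is added. The small downside is that allocation and the first prescription wait until the day 0 measurements are done.

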### 2.3 Ethics and dissemination

This clinical trial has been approved by the Ethics Committee of Shenzhen Hospital of Guangzhou University of Chinese Medicine (Futian) (Project number: GZYLL(KY)-2021–025).

Prior to signing the informed consent form, the investigator will provide the patient with a detailed description of the process, potential risks and benefits of participating in the study. Participants will sign an informed consent form and allow the study results to be published in a peer-reviewed journal. All participants’ personal data will be kept confidential during and after the trial. Only authorized researchers have access to all data on participants.

### 2.4 Inclusion criteria

1) All participants must meet the individual diagnostic criteria for T2DM and NAFD. The diagnostic criteria for T2DM (American Diabetes Association Professional Practice Committee, 2022) includes:• Fasting plasma glucose (FPG) ≥126 mg/dl (7.0 mmol/L) or 2-h plasma glucose (2-h PG) ≥200 mg/dl (11.1 mmol/L) during an oral glucose tolerance test or HbA1c ≥ 6.5% (48 mmol/mol).• Typical symptoms of hyperglycemia (excessive thirst, polyuria, weight loss, hunger, pruritus, or coma) or hyperglycemic crisis plus a random plasma glucose (PG) ≥200 mg/dl (11.1 mmol/L). Patients without typical symptoms of diabetes need to be re-examined for confirmation. Fasting state: no intake of calories for at least 8 h; random plasma glucose: blood glucose at any time of day, regardless of the last meal time (cannot be used to diagnose abnormal fasting blood glucose or abnormal glucose tolerance). The diagnostic criteria for NAFLD (European Association for the Study of the Liver (EASL) et al., 2016) (Chalasani et al., 2018) requires:• Evidence of excess liver fat accumulation (hepatic steatosis) on ultrasound imaging.• Exclusion of excessive daily alcohol consumption ≥30 g for men and >20 g for women (Ratziu et al., 2010).• Acute or chronic viral hepatitis (e.g., hepatitis C), autoimmune hepatitis, hemochromatosis, Wilson’s disease, alcoholic liver disease, drug-induced liver disease, liver cirrhosis, inborn errors of metabolism (e.g., cholesterol ester storage disease), or other causes of chronic liver disease.2) All participants must meet the diagnostic criteria for heat stagnation syndrome in the liver and stomach in accordance with the Guidelines for Clinical Research of Chinese Medicine (Zheng, 2002) outlined below.• Any two main symptoms including dry mouth, bitter and sticky mouth, heaviness in the head and body, and/or obesity• Any two secondary symptoms including fullness and distention of the chest or abdomen, upset or irritable demeanor, rapid digestion of food and polyorexia, deep-colored or turbid urine, and/or unpleasant or constipated stools.• Tongue condition: red tongue, yellow fur.• Pulse condition: stringy and rapid pulse or slippery and rapid pulse.3) Participants should be between the ages of 20 and 75 years.4) The experimental group should not have taken traditional Chinese medicine for diabetes and NAFD orally for at least 2 weeks before enrollment.

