### 2.10 Sample size calculation

In a previous study (Xu, 2017), JTTF reduced HbA1c levels in diabetic patients with heat stagnation in liver and stomach after 12 weeks of treatment (treatment group: 6.94±0.88%, control group: 7.64±0.72%, mean difference between the two groups: 0.7%). Considering a type I error of 5% (α = 0.05) and a power of 85%, the experimental and control groups were allocated at a ratio of 1:1. The sample size was calculated using Power Analysis and Sample Size (PASS) software (version 15.0); a total of 76 patients will be required. According to the dropout rate of 20%, we set the final sample size to 96, with 48 patients in each group, considering the number of dropout samples.

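### Inclusion criterion 4 restricts prior traditional Chinese medicine in the experimental group only, which conflicts with randomising patients who are already enrolled

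*Protocol article*

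**What the plan says.** Section 2.4 lists four inclusion criteria, and the first three cover everyone:

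- Criterion 1: "All participants must meet the individual diagnostic criteria for T2DM and NAFD".
- Criterion 2: "All participants must meet the diagnostic criteria for heat stagnation syndrome in the liver and stomach".
- Criterion 3: "Participants should be between the ages of 20 and 75 years".

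Criterion 4 changes subject: "The experimental group should not have taken traditional Chinese medicine for diabetes and NAFD orally for at least 2 weeks before enrollment".

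Section 2.9 gives the order of events: "Patients successfully enrolled in the study will be randomly assigned to either the treatment or control group at a 1:1 ratio". It also states: "Since this trial is an open-label study, participants and physicians will be aware of the assignment protocol". Section 2.8.2 defines the endpoints: "The primary outcome is change in visceral fat area (VFA) and TCM syndromes efficacy score scale".

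**The concern.** An entry criterion has to be decidable before the arm is known. A criterion about the experimental group is not, because no such group exists at screening. Staff who follow the text literally could apply it only after opening the envelope, and only to patients allocated to JTTF.

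That would remove recent TCM users from one arm and leave them in the other, undoing for that factor the balance that randomisation gives. The factor matters here because it is recent use of the same class of treatment as the one on test. Both primary outcomes are changes from baseline, and the metabolomics comparison also starts from baseline samples. A one-sided difference in recent treatment could affect all three.

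**Working it through.** The article gives no figure on this point to reproduce, so the check is mainly a comparison of passages.

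**Step 1. Is there a matching restriction for controls?** None appears in the exclusion criteria (2.5), the drop-out criteria (2.6) or the intervention section (2.7). Criterion 4 is the only statement on TCM use before enrolment.

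**Step 2. Can criterion 4 be applied in the stated order?** Section 2.9 goes from enrolment to randomisation. Criterion 4 needs the arm, and the arm does not exist until enrolment is complete. Both cannot be followed literally.

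**Step 3. Does anything else prevent use after allocation?** Table 1 ticks the eligibility check, consent and allocation in the same column (day -14 to 0), so the schedule does not separate them. Clinicians hold the envelopes and the trial is open label (2.9). Table 1 then places visceral fat area, TCM symptoms and the serum and urine samples at day 0±2. The text does not require use after allocation, but does not rule it out.

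**Step 4. Illustration of the numbers affected.** Inputs: 48 per arm (section 2.10) and an assumed share q of candidates with recent oral TCM use. The article does not give q. Section 2.11 recruits mainly from the endocrinology department of a Chinese medicine university hospital, so recent use is plausible but not quantified. If criterion 4 is applied to one arm after allocation:

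- JTTF arm remaining = 48 × (1 − q)
- Recent users kept in control = 48 × q

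| q (assumed) | JTTF arm left | Recent users among 48 controls |
|---|---|---|
| 5% | 45.6 | 2.4 |
| 10% | 43.2 | 4.8 |
| 20% | 38.4 | 9.6 |
| 30% | 33.6 | 14.4 |

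**Step 5. Illustration of the shift in the control mean.** Let c be the change over follow-up, in SD units, that prior or continuing TCM causes in those users. The control mean change shifts by q × c. With q from 10 to 30% and c from 0.25 to 0.5 SD, the shift runs from 0.10 × 0.25 = 0.025 SD to 0.30 × 0.5 = 0.15 SD. The article gives neither q nor c, and c may have either sign:

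- If controls stop their TCM at entry and its effect wanes, the shift favours JTTF.
- If controls continue it with benefit, the contrast shrinks and the shift works against JTTF.

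**The case against.** The strongest reply is that this is a slip of wording. Criterion 4 stands under the inclusion criteria, is dated to before enrolment, and section 2.9 randomises only enrolled patients. If sites keep to that order, the criterion cannot be applied by arm, and the authors probably meant participants in general. The drop-out criteria do not name prior TCM use, and no section tells staff to remove an allocated JTTF patient for it.

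Much of this stands. A reader might infer that the randomised groups are not comparable. The documents do not support that as a fact: it follows only if the criterion is applied after the arm is known.

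A reader might also infer that the bias favours JTTF. That would require that the earlier TCM worked, that controls stop it at entry, and that its effect wanes within 12 weeks. None of these is stated, and controls who continue would pull the result the other way.

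Nor is an inflated type I error shown. With 38 per arm (76 in total, section 2.10), the standard error is √(2/38) = 0.229 SD. At a two-sided 5% level, a shift of 0.10 SD (20% × 0.5 SD) gives a rejection probability of about 7.2%, but a shift of 0.04 SD (20% × 0.2 SD) gives about 5.4%. The answer depends on two assumed inputs.

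The reply does not remove the conflict. Even on the benign reading, staff have a published criterion that they cannot apply at screening, and a reader cannot tell whether the restriction held for controls.

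**Conclusion.** The point holds as a conflict between sections 2.4 and 2.9. One eligibility rule is worded for a single arm, while the other three criteria and the order of randomisation require rules that hold for everyone. This is a stated rule with the wrong scope, not a detail left to a fuller document.

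The consequence is conditional. If the rule is applied as written, after allocation, the arms lose comparability at baseline in visceral fat area, TCM score and metabolomics, with a bias of unknown direction and size. If eligibility is settled before randomisation, no imbalance arises from this source and only the wording is at fault. The conclusion rests on the text alone. The counts and shifts in the working rest on an assumed share of users and an assumed effect, and only show what could be at stake.

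**What to change.** Reconcile sections 2.4 and 2.9. Reword criterion 4 so that the protocol's own prior-TCM restriction applies identically to all participants, and state that it is checked before randomisation. This changes only whom the criterion covers.

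Section 5 reports that recruitment was under way at submission. For patients already enrolled, record TCM use before enrolment in both arms, report it by arm at baseline, and exclude no one from one arm only.

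The cost is a short wording amendment, one recorded item per enrolled patient, and slightly fewer eligible candidates overall. There is a single candidate pool before randomisation, so the loss does not fall on one arm.

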### 2.5 Exclusion criteria

1) Patients with liver or kidney dysfunction: aspartate transaminase [AST] or alanine transaminase [ALT] >2.5 times the normal upper limit or creatinine >115 μmol/L.2) Patients with chronic diseases, such as hypertension, cardiovascular, cerebrovascular, autoimmune diseases, chronic kidney diseases and psychiatric diseases who cannot follow research procedures.3) Patients who are using insulin.4) Allergic constitution or a history of drug allergies.5) Pregnant and lactating women.6) Patients who participated in other clinical studies within the preceding three months.

